### Primary outcome

The primary outcome of the present trial is ED symptomatology at the end of the intervention assessed with the child version of the Eating Disorder Examination-Questionnaire (ChEDE-Q; [43]). The ChEDE-Q measures disordered eating over a 28-day period and includes 28 items and four subscales (Eating Concern, Shape Concern, Weight Concern, and Dietary Restraint) as well as a global score, which is an average of the subscales.

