### Sample size calculation

We assume a small to medium effect (superiority of the two intervention groups over the control condition) on ED symptomatology. Repeated measures analysis of variance (ANOVA) will be conducted (time*group interaction, alpha = 5%). Assuming an effect of *f* = 0.15, a dropout rate of 20%, and correlations of 0.1 among repeated measures, 309 subjects need to be recruited (103 per group) to test the global hypothesis with 90% power. In case of significant findings for the main effect of study group, the proposed sample size will allow for post hoc pairwise group comparisons at a power above 80%.

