### Statistical analysis

Primary data analyses will be based on the intention-to-treat (ITT) population; i.e., all participants randomized to one of the three study conditions will be included in the primary outcome analysis. Missing data patterns will be explored. Multiple imputations will be applied to impute missing data.

Repeated measures ANOVA will be conducted (time*group interaction, alpha = 5%) to test the primary hypothesis, i.e., differences in efficacy between the interventions. For the primary outcome, only the baseline and the post assessment after 6 weeks will be considered. In case of statistically significant differences, post hoc pairwise group comparisons will be conducted (Bonferroni correction). Repeated measures ANOVA will also be conducted to determine the effect of the interventions on metric secondary outcomes. Post-intervention symptom courses will be analyzed applying mixed effects models. In order to investigate gender-specific efficacy, multifactor ANOVAs will be conducted. Fisher’s exact test will be applied to compare actual help-seeking between the groups.

For the health economic evaluation, data on the costs of interventions and efficacy will be used to determine the incremental cost-effectiveness ratio (ICER) of the interventions. The ICER will provide the additional costs in monetary terms of the respective programs to be spent for gaining an additional outcome unit. Cost-utility analyses will provide information on cost per quality-adjusted life years (QALYs) gained by the various interventions. Bootstrapping procedures will be applied to provide cost-effectiveness planes and acceptability curves.

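### The primary time-by-group test on two time points is a change-score comparison; at the plan's own correlation of 0.1 its variance is 1.8 times that of a baseline-adjusted comparison

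*Protocol article*

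**What the plan says.** The Primary outcome section defines the endpoint at a single time: "The primary outcome of the present trial is ED symptomatology at the end of the intervention", measured with the ChEDE-Q. The Statistical analysis section fixes the test: "Repeated measures ANOVA will be conducted (time*group interaction, alpha = 5%) to test the primary hypothesis". It then limits the data: "For the primary outcome, only the baseline and the post assessment after 6 weeks will be considered". Significant results lead to Bonferroni-corrected pairwise comparisons, and missing values are multiply imputed.

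The Sample size calculation section uses the same interaction test. Its inputs are "Assuming an effect of *f* = 0.15" and "a dropout rate of 20%, and correlations of 0.1 among repeated measures, 309 subjects need to be recruited (103 per group"), for 90% power on the global hypothesis. It adds that pairwise comparisons will have power above 80%.

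Nowhere is baseline ChEDE-Q named as a covariate. The mixed effects models in the Statistical analysis section are for symptom courses after the intervention, not for the primary test.

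**The concern.** With one pre- and one post-randomisation score, the time-by-group interaction asks whether the mean of (6 weeks minus baseline) differs between arms. Subtracting baseline removes the part of the 6-week score that baseline predicts, but it also adds the baseline score's own noise. When the two scores correlate weakly, the added noise outweighs what is removed. The protocol plans on a correlation of 0.1, which is well into that range.

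At stake is the precision of the primary comparison and of the module-versus-ProYouth contrasts. The comparator is an active program, and the Discussion warns that study dropout may be high, so a real module effect could be missed that the same data would show under a better analysis.

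**Working it through.** **Inputs from the protocol.** Three arms at 1:1:1; two time points in the primary test; f = 0.15; r = 0.1; alpha 5%; 20% dropout; N = 309. I assume equal SD σ at both visits.

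**1. Reproduce the plan's figure.** For the within-between interaction, the noncentrality is λ = f²·N·m/(1−r), with m = 2 and df (2, N−3).
- N = 257: λ = 0.0225 × 257 × 2/0.9 = 12.85, power 0.901. This is the smallest N reaching 90%.
- 257 × 1.2 = 308.4, rounded up to 309. The stated size is reproduced, so the calculation was made for this test.
- With 20% lost, 309 × 0.8 ≈ 247 remain: λ = 12.35, power 0.889.

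**2. Variances.**
- Change score: 2(1−r)σ² = 2 × 0.9σ² = 1.80σ².
- 6-week score with baseline as covariate: (1−r²)σ² = (1−0.01)σ² = 0.99σ².
- 6-week score alone: 1.00σ².
- Change/ANCOVA = 2(1−r)/(1−r²) = 2/(1+r) = 2/1.1 = 1.82. A simulation with 82 per arm gave 1.82.

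**3. Planned effect in SD units.** Suppose both modules share the same advantage d over ProYouth at 6 weeks and none at baseline. With n per arm and variance Vσ², λ = n(2/3)d²/V. Setting V = 2(1−r), n = N/3 and equating to the formula in step 1 gives d² = 18f², so d = 0.15 × √18 = 0.636 SD.

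**4. Global power at 247 completers, r = 0.1.**
- Planned test: λ = (247/3)(2/3)(0.405)/1.80 = 12.35, power 0.889.
- ANCOVA: the same with V = 0.99 gives λ = 22.45, power 0.992.
- For 90% power, ANCOVA needs about 143 evaluable participants instead of 257.

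**5. Module versus ProYouth, d = 0.636, 82.4 per arm, r = 0.1** (two-sample t test).

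| Alpha | Change score | ANCOVA |
|---|---|---|
| 0.05, uncorrected | 0.857 | 0.983 |
| 0.025, two comparisons | 0.782 | 0.967 |
| 0.0167, three comparisons | 0.734 | 0.953 |

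**6. Sensitivity to r and d, global power at 247 completers.** The values r = 0.3, 0.5 and 0.7 and d = 0.50 and 0.35 are my assumptions; the protocol gives none of them. Each cell is change score / ANCOVA.

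| r | Variance ratio | d = 0.636 (planned) | d = 0.50 | d = 0.35 |
|---|---|---|---|---|
| 0.1 | 1.82 | 0.889 / 0.992 | 0.69 / 0.92 | 0.39 / 0.64 |
| 0.3 | 1.54 | 0.953 / 0.995 | 0.80 / 0.94 | 0.48 / 0.67 |
| 0.5 | 1.33 | 0.991 / 0.999 | 0.92 / 0.97 | 0.63 / 0.76 |
| 0.7 | 1.18 | >0.999 / >0.999 | 0.99 / >0.99 | 0.85 / 0.91 |

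**7. Unequal SDs.** With baseline SD s₀ and 6-week SD s₁, change variance = s₁²(1−r²) + (s₀−r·s₁)². The second term cannot be negative, so the adjusted analysis is never the noisier one, apart from one degree of freedom spent on the slope. If s₀ = 0.8s₁ (assumed) and r = 0.1, change variance is (1 + 0.64 − 0.16)s₁² = 1.48s₁², and the ratio is 1.48/0.99 = 1.49.

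**The case against.** The strongest reply is that nothing here is invalid. Under randomisation the change-score test controls type I error and is unbiased. The sample size was computed for this same test, and on the protocol's assumptions its global power is 0.889 at 247 completers, close to the stated 90%. ANCOVA would therefore add power beyond the target rather than repair a failure to reach it. That stands.

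Second, the factor of 1.8 depends on a planning correlation of 0.1 and on equal SDs, and the protocol reports no observed correlation. With r = 0.5 at the planned effect, both analyses exceed 0.99. Selecting some participants on a high Weight Concerns Scale score may also narrow the baseline SD and lower the ratio. This limits the size of the gain but not its direction. The planned effect of 0.636 SD is also large for what the protocol calls small to medium; at smaller true effects the gain is material even at r = 0.5.

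Third, the pairwise shortfall is partly a multiplicity matter. The Discussion treats the comparison of the two modules as exploratory, and with two comparisons the figure is 0.78 rather than 0.73. The protocol does not say whether its figure of above 80% allows for the correction. Uncorrected, the planned test gives 0.86. This is fair, but both corrected figures are below 80%, and both exceed 95% with baseline adjustment.

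Finally, over-correction of a chance baseline imbalance averages out over randomisations and is already counted in the variance ratio. It is not a further harm.

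**Conclusion.** The concern holds. The primary test is a comparison of raw change scores. At the protocol's own correlation and with equal SDs, its variance is 1.82 times that of a baseline-adjusted comparison, and 1.8 times that of the 6-week score alone. At the planned effect with 247 completers, this costs about 10 points of global power (0.889 against 0.992) and about 22 points of pairwise power with three-way Bonferroni correction (0.734 against 0.953).

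These sizes rest on r = 0.1, equal SDs and equal benefit from both modules; a higher correlation narrows the gap. The direction does not depend on those assumptions. This is a loss of precision, not bias, but it is avoidable: baseline ChEDE-Q is collected before randomisation, and the adjusted analysis directly targets the endpoint as the protocol defines it.

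**What to change.** Replace the primary analysis with an ANCOVA of the 6-week ChEDE-Q global score. Use study arm as factor and baseline ChEDE-Q as covariate, with gender added because randomisation is stratified by it. Fit it within the planned multiple imputation. A mixed model with the baseline means constrained equal across arms would serve equally well. Report each module-minus-ProYouth adjusted mean difference with its confidence interval. Use the same model, with contrasts at each visit, for metric secondary outcomes that have a baseline value. Keep the repeated measures ANOVA as a sensitivity analysis.

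The cost is a change to the analysis section and the SAP. Recruitment began in November 2018, so it should be a dated amendment made before database lock and before any outcome comparison by arm. It needs no further data or participants, and the 309 can stand.

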### Secondary outcomes

Secondary outcomes include ED symptomatology at 6, 12, and 24 months follow-up measured with the ChEDE-Q and the SEED. Additional outcomes are body dissatisfaction, appearance ideal internalization, ED-related stigma, and ED-related help-seeking at the end of the intervention and at 6 months follow-up. Body dissatisfaction is measured with the 8-item version of the widely used Body Shape Questionnaire (BSQ; [44, 45]). Research on the brief version (BSQ-8C) demonstrated good psychometric properties and sensitivity to change [46]. Items are rated on a 6-point Likert scale from 1 = “never” to 6 = “always”, with higher scores indicating higher levels of body dissatisfaction. Appearance ideal internalization is assessed using the internalization subscale of the German version of the Sociocultural Attitudes Towards Appearance Questionnaire (SATAQ-G) for female and male participants, respectively [47]. It consists of 6 items reflecting the adoption of the thin or muscular ideal as a personal standard. Stigma is measured with the ED-specific version of the Universal Stigma Scale (USS; [48]). The USS is an 11-item instrument. It consists of two subscales (impairment/distrust, blame/personal responsibility), with internal consistencies between 0.72 and 0.83 across different samples [48]. ED-related help-seeking is measured with an ED-specific version of the General Help-Seeking Questionnaire (GHSQ; [49]), a frequently used measure for help-seeking for psychological complaints. Acceptance of the online interventions (ProYouth, ProYouth-DISS, ProYouth GROUP) will be assessed with the German version of the Client Satisfaction Questionnaire (ZUF-8; [50]) adapted for the online setting. The ZUF-8 measures participants’ satisfaction with the intervention. Finally, compliance with the interventions and utilization of the various modules will be analyzed based on automatically recorded server logs.

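### The follow-up outcomes at 6, 12 and 24 months are not tied to an arm contrast at those times, and two plausible readings of the named analyses would answer a different question

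*Protocol article*

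**What the plan says.** Under Secondary outcomes, the protocol article defines outcomes at time points: "Secondary outcomes include ED symptomatology at 6, 12, and 24 months follow-up measured with the ChEDE-Q and the SEED". Body dissatisfaction and appearance ideal internalization are listed with "ED-related stigma, and ED-related help-seeking at the end of the intervention and at 6 months follow-up".

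Under Statistical analysis, two methods bear on these outcomes:
- "Repeated measures ANOVA will also be conducted to determine the effect of the interventions on metric secondary outcomes". The occasions and the tested term are not given.
- "Post-intervention symptom courses will be analyzed applying mixed effects models". The occasions, the handling of baseline and the contrast are not given.

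The interaction term is written out for the primary hypothesis: "Repeated measures ANOVA will be conducted (time*group interaction, alpha = 5%) to test the primary hypothesis". The limit to two occasions is also written for the primary outcome: "For the primary outcome, only the baseline and the post assessment after 6 weeks will be considered". No sentence links a follow-up outcome to a difference between arms at that follow-up.

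**The concern.** An outcome defined at 24 months poses the question whether the arms differ at 24 months. The two named methods can each be run in a way that tests something else.

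- A comparison of post-intervention courses asks whether arms change in parallel after week 6. A fully maintained benefit gives parallel courses, so it looks like no effect. A fading benefit gives the add-on arm the worse course.
- A time-by-group interaction over all occasions asks whether the whole profiles are identical. A difference at week 6 alone breaks that null, so a significant result says nothing about a particular follow-up.

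The Background counts long-term effects among the open questions in the field, and the Discussion presents long-term follow-up as a strength. With the contrast left open, a lasting effect could be reported as absent, or a transient one as lasting.

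**Working it through.** **Inputs from the article.** Three arms, 1:1:1 allocation, alpha 5%, 90% power. "Assuming an effect of *f* = 0.15". "a dropout rate of 20%, and correlations of 0.1 among repeated measures". Recruitment target 309 (103 per group).

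**Reproducing the plan's figure.** For the within-between interaction, λ = N·f²·m/(1−ρ), with df (k−1)(m−1) and (N−k)(m−1). With k = 3, m = 2, f = 0.15 and ρ = 0.1, 90% power needs N = 257. Then 257 × 1.2 = 308.4, rounded up to 309. So the plan's f is on the two-occasion interaction scale. With 20% lost, 309 × 0.8 = 247, or about 82 per arm.

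**Effect in SD units (assumption: both add-ons benefit equally by d over ProYouth).** Arm deviations are d × (2/3, −1/3, −1/3), with squared sum 2d²/3. For two occasions f² = d²/18, so d = 0.15 × √18 = 0.636 SD and 2d²/3 = 0.27. For d = 0.4 it is 0.1067.

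**Further assumptions.** Complete data on 82 per arm, unit SD and equal correlation ρ between all occasions. If the effect is present at q of the m analysed occasions, the interaction has λ = n·(2d²/3)·q(m−q)/m/(1−ρ).

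**1. Group-by-time on the four post-intervention occasions, benefit fully maintained.** q = m = 4, so λ = 0 and the rejection rate is 5.0% at every ρ.

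**2. Group-by-time over all five occasions.**
- Effect at week 6 only: q(m−q)/m = 1 × 4/5 = 0.8, so λ = 82 × 0.27 × 0.8/0.9 = 19.68 and rejection is 90.8%.
- Effect fully maintained: 4 × 1/5 = 0.8, so λ is again 19.68 and rejection is again 90.8%. The omnibus test cannot tell the two situations apart.
- Baseline, 6 weeks and 6 months, effect at week 6 only: λ = 82 × 0.27 × (2/3)/0.9 = 16.4, rejection 91.6%.

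**3. Group term of the post-intervention model (average over four occasions).** For a maintained benefit its power is about 100%. For a 6-week-only effect, λ = 82 × 0.27 × (1/16)/[(1 + 3 × 0.1)/4] = 4.26 and it rejects in 43%, because week 6 is part of the average.

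**4. Baseline plus one follow-up.** m = 2. For a maintained benefit, λ = 82 × 0.27 × 0.5/0.9 = 12.3 and power is 88.7%. For a 6-week-only effect, rejection is 5.0%. This form does test the follow-up.

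**5. Baseline as covariate, same follow-up.** λ = n·(2d²/3)/(1−ρ²), with df 2 and 242. This stands in for the global arm test at one follow-up from the proposed mixed model under complete data.

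| d, ρ | λ, baseline + follow-up ANOVA | Power | λ, baseline-adjusted | Power |
|---|---|---|---|---|
| 0.636, 0.1 | 12.3 | 88.7% | 82 × 0.27/0.99 = 22.4 | 99.2% |
| 0.4, 0.1 | 82 × 0.1067 × 0.5/0.9 = 4.86 | 48.7% | 82 × 0.1067/0.99 = 8.84 | 75.7% |
| 0.4, 0.5 | 82 × 0.1067 × 0.5/0.5 = 8.75 | 75.3% | 82 × 0.1067/0.75 = 11.66 | 86.9% |

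The ratio of the two λ values is 2/(1+ρ), that is 1.82 at ρ = 0.1 and 1.33 at ρ = 0.5. The advantage shrinks as the correlation rises.

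**The case against.** The strongest reply is that the article fixes no wrong test. It does not say that the secondary ANOVA uses all occasions. The primary outcome is defined at one time point and analysed on baseline plus that point, so the same template can be carried to each follow-up. The word *only* may be there simply because the ChEDE-Q is measured again later. Likewise, a mixed model of post-intervention symptoms usually has a group term, and time-specific contrasts can be drawn from it. Even if both doubtful readings applied, the two results together would help: a maintained benefit gives a significant ANOVA with a flat course comparison, and a fading one gives a significant result in both. Finally, this is a condensed article, and model terms for secondary outcomes are often set out in an analysis plan that is not shown.

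Much of this stands. A reader might infer that neither named analysis can test the arms at 6, 12 or 24 months. The text does not support that, since the baseline-plus-one-follow-up ANOVA fits the wording and works (step 4).

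Two things remain. The article's stated target for the later period is the course, whereas its listed outcome is the level at a time point, and the group term averaged over occasions does not bridge the two (step 3). And even the favourable reading is a change-type analysis that gives up power against baseline adjustment (step 5). So the remedy does more than supply omitted detail.

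**Conclusion.** The point holds in conditional form. The article ties neither analysis to an arm contrast at 6, 12 or 24 months. Judged by group-by-time after week 6, a fully maintained benefit is flagged in 5% of trials. Judged by an all-occasion interaction, a 6-week-only effect is flagged in about 91% at 0.636 SD and ρ = 0.1. That second reading is suggested by the primary-outcome sentence but not stated. On the valid reading, the loss against baseline adjustment is 88.7% versus 99.2% at 0.636 SD, and 48.7% versus 75.7% at 0.4 SD.

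These figures rest on equal benefit in both add-ons, complete data on 82 per arm and equal correlation across occasions. The 0.4 SD effect and ρ = 0.5 are illustrative, not from the article. Attrition by 24 months may exceed the single 20% that the article gives, which would lower all the power figures. The primary analysis at 6 weeks is not affected. The change is worth making for the secondary outcomes.

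**What to change.** For each metric follow-up outcome, specify one mixed model with:
- all post-randomization assessments at which the outcome is measured (6 weeks, 6, 12 and 24 months) as outcomes;
- the baseline score as covariate;
- time as a category, with arm-by-time terms.

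Base follow-up conclusions on the estimated add-on minus ProYouth difference at each follow-up, with its 95% confidence interval. Keep the comparison of post-intervention courses as a description of maintenance only. State that a non-significant course difference does not show the absence of a lasting effect, and that a significant overall interaction does not show an effect at follow-up.

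The cost is wording. No data, visits or participants are added. The small downside is more contrasts to report for each secondary outcome. If the sponsor already intends this analysis, a sentence saying so is enough.

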### Recruitment and study procedures

The ProHEAD Consortium will recruit a school-based sample of 15,000 C&A aged 12 or older in grades 6–13 in five regions of Germany (Hamburg, Heidelberg, Leipzig, Marburg, Schwäbisch Gmünd). The procedures with respect to selection of schools are described in the study protocol of sub-project 1 of the ProHEAD Consortium [29].

Written informed consent will be obtained from C&A and their legal guardians prior to inclusion into the project. As part of the ProHEAD CP, assessments of sociodemographic information, healthcare utilization, help-seeking, and a broad variety of mental health problems and health-risk behaviors will be included in the screening and the two annual follow-ups. These three annual assessments will be conducted electronically via the ProHEAD online platform in the computer rooms of the respective schools (for details on the instruments used at the school-based assessments, see the study protocols of the other ProHEAD sub-projects in this issue [29–32]). Based on the screening results, each participant will be allocated to one of the five ProHEAD RCTs. Participants who meet eligibility criteria for more than one RCT will be randomly allocated to one of the sub-projects.

Participants assigned to the present ED trial will receive an email inviting them to register for the study. In order to enroll, they will need to click on a link in this email to activate their user account and to complete a trial-specific baseline online assessment. Upon completion of this assessment, they will be randomized to one of the three study arms and then have access to the respective intervention (ProYouth, ProYouth-DISS, or ProYouth-GROUP) for a duration of 6 weeks. Trial-specific post and follow-up assessments will be conducted online 6 weeks after randomization and 6 months later (Fig. 1).

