### Randomization and blinding

Eligible C&A will be randomized to one of the three interventions based on an allocation sequence derived from a computerized random number generator at a 1:1:1 ratio. The allocation scheme is embedded into the ProHEAD online platform; i.e., participants are automatically assigned to one of the study arms and informed electronically about the outcome without researchers having access to the allocation scheme. Randomization will be stratified by gender. Due to the study characteristics, blinding of participants and/or online counselors is not possible because participants will be informed as to which intervention they were assigned, and counselors need to provide guidance accordingly.

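### The only named analysis of actual help-seeking is an unadjusted three-arm Fisher's exact test: valid, but it uses neither gender nor help-seeking at screening and gives no contrast with ProYouth

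*Protocol article*

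**What the plan says.** All references are to the protocol article.

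- **Test (Statistical analysis).** Fisher's "exact test will be applied to compare actual help-seeking between the groups". No stratification, covariate or effect measure is attached to it.
- **Outcome (Secondary outcomes).** The additional outcomes include "ED-related help-seeking at the end of the intervention and at 6 months follow-up". On the instrument: "ED-related help-seeking is measured with an ED-specific version of the General Help-Seeking Questionnaire". The article does not define how a yes/no variable for actual help-seeking is formed, or at which visit it is tested.
- **Randomization (Randomization and blinding).** "Randomization will be stratified by gender", using a "computerized random number generator at a 1:1:1 ratio".
- **Information before randomization (Recruitment and study procedures).** The consortium's assessments cover "help-seeking, and a broad variety of mental health problems and health-risk behaviors will be included in the screening and the two annual follow-ups". Screening precedes randomization.
- **Missing data (Statistical analysis).** "Multiple imputations will be applied to impute missing data". The sentence is not limited to any outcome, but it closes the paragraph on the primary intention-to-treat analysis.
- **Gender elsewhere (Statistical analysis).** Multifactor ANOVAs are planned for gender-specific efficacy. They do not adjust the Fisher test.

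**The concern.** Rationale and objectives sets out to compare each enhanced version with ProYouth alone. Help-seeking is a named secondary outcome and part of the consortium's name, and the last ProYouth-GROUP session is devoted to it. A single omnibus p-value over a 3x2 table does not say which add-on changed help-seeking, in which direction, or by how much.

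The test also leaves aside two pieces of information that exist before randomization: the stratification factor and a screening measure of help-seeking. If either predicts the outcome, an analysis that uses it is more sensitive at no extra data cost. Fisher's test is moreover conservative when events are few, which is plausible for help-seeking in a sample screened to exclude clinically relevant impairment.

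Finally, the Discussion warns that dropout may be high. If imputation is to cover this outcome, a method that yields an estimate and a standard error fits far more easily than a 3x2 Fisher test.

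**Working it through.** **1. Inputs.** The article gives no event rate, effect or power for help-seeking, so there is no planned figure to reproduce. Its sample size (309, or 103 per group) and its 20% dropout rate belong to the primary outcome. Borrowing them gives 103 × 0.80 = 82.4, taken as 82 per arm. Everything else below is an assumption: event rates, an odds ratio of 2.5, the gender mix, the share with prior help-seeking, and predictor strength.

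**2. True size of the nominal 5% test.** Size = sum over the total number of events s of P(s) × P(table rejected | s), by full enumeration of all tables with 82 per arm and a common event rate in every arm.

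| Event rate | Three-arm Fisher | Two-arm Fisher |
|---|---|---|
| 3% | 2.5% | 0.8% |
| 5% | 3.9% | 1.7% |
| 10% | 4.5% | 2.9% |

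The three-arm column is the natural reading of a comparison between the groups. The two-arm column applies only if pairwise Fisher tests were added, which the article does not say.

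**3. Power, three arms.** The data model was logit P(help-seeking) = intercept + arm + 0.7 × gender + b × prior help-seeking. It assumed 80% girls, 20% with prior help-seeking, and an odds ratio of 2.5 for both add-ons. Fisher's test was compared with a covariate-adjusted 2-df score test.

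| Predictor strength | Control rate | Fisher | Adjusted | Gain |
|---|---|---|---|---|
| Strong (b = 2.0), 4,000 runs | 11% | 42% | 48% | 6 points |
| Strong (b = 2.0), 4,000 runs | 17% | 56% | 63% | 7 points |
| Strong, repeat with 3,000 runs | 11% | 44% | 50% | 6 points |
| Strong, repeat with 3,000 runs | 17% | 54% | 62% | 8 points |
| Weaker (b = 1.0) | – | – | – | about 1 to 1.5 points |

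In the 4,000-run simulation, null rejection was 4.5% to 5.5% for the adjusted test and 4.2% to 4.6% for Fisher. The gain therefore does not come from an inflated error rate.

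**4. Sensitivity to the set-up.** A two-arm comparison took 75% girls, 15% with prior help-seeking, a likelihood-ratio test and control rates of 8% to 29%. Power was 37% to 69% for Fisher and 47% to 76% for the adjusted test, a gain of about 8 to 15 points. Part of that reflects the stronger conservatism of the two-arm Fisher test, whose null rejection was 1.9% to 3.3% (adjusted test: 4.3% to 5.7%). It is not the size of the loss for the three-arm test as written.

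**5. Pooling.** Rubin's rules need an estimate and its variance from each imputed dataset. A logistic model supplies a log odds ratio and standard error per add-on. A 3x2 Fisher test supplies only a p-value, so it would need a special rule for combining p-values.

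**The case against.** The strongest reply is that nothing here is wrong. Fisher's test keeps its level under gender-stratified randomization, and ignoring the strata costs efficiency only. That stands.

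A reader might go further than the documents allow in several ways:

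- **That the test cannot be combined with multiple imputation.** Rules for pooling p-values and test statistics exist, and the planned multi-df ANOVA test needs such rules as well. Only direct use of Rubin's rules is ruled out.
- **That the plan contradicts itself by analysing completers only.** No sentence says so. The imputation sentence sits with the primary analysis, and applying it to help-seeking is a reading.
- **That no effect estimate will be reported.** Naming a test does not exclude one, and an article may leave effect measures to the statistical analysis plan.
- **That help-seeking receives only a yes/no test.** Repeated measures ANOVA is assigned to metric secondary outcomes, and a metric GHSQ score would fall there. Fisher's test is tied to actual help-seeking.
- **That screening help-seeking is the baseline value of the outcome.** The article does not show that they are the same variable. A covariate need not be identical to the outcome, but its predictive strength is unknown.

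The objection that a model is fragile with few events also has force. At a 3% rate, 3 × 82 × 0.03 gives about 7 events for a model with five parameters. The chance that at least one arm has none is 1 − (1 − 0.97^82)^3 = 23%. This is a reason for penalized likelihood from the outset and for keeping the exact test alongside.

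**Conclusion.** The point holds as an optional improvement to one secondary analysis. The only method named for actual help-seeking is valid, but it leaves pre-randomization information unused and does not address each add-on against ProYouth.

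The size is modest. The three-arm test is mildly conservative (2.5% to 4.5% true size at event rates of 3% to 10%). Adjustment is worth about 1 point of power if prior help-seeking predicts weakly and about 6 to 8 points if it predicts strongly, at an odds ratio of 2.5 and 82 per arm. All of these rates and strengths are assumptions. The case for per-arm contrasts, and for estimates that pool directly, does not depend on them. The primary outcome is unaffected.

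**What to change.** In Statistical analysis, make the main analysis of actual help-seeking a logistic regression on arm, gender and help-seeking at screening, or on arm and gender alone if the screening item proves unsuitable. Settle that choice before the outcome data are seen. Fit the model with Firth's penalized likelihood throughout, so that no switch depends on the observed number of events. Report odds ratios or risk differences for each add-on versus ProYouth with 95% confidence intervals, and pool by Rubin's rules wherever imputation is used. Keep Fisher's test as a sensitivity check.

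The cost is a sentence or two of text and slightly more programming, on data already being collected. The downside is a model-based rather than an exact p-value when events are very few, which the retained Fisher test helps to guard against.
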